2.3 RISK/BENEFIT ASSESSMENT

2.3.1 KNOWN POTENTIAL RISKS

Plasma represents a licensed blood product, for which the risks are well described. These are the risks

associated with the administration of plasma, including allergic reaction and viral infections. There is also the risk that convalescent plasma may be ineffective.

2.3.2 KNOWN POTENTIAL BENEFITS

COVID-19 convalescent plasma has not yet been demonstrated to provide clinical benefit in patients

affected by this disease.

2.3.3 ASSESSMENT OF POTENTIAL RISKS AND BENEFITS

The safety profile of plasma administration is well established. Taking into account the preliminary data

available on the possible benefit of COVID-19 plasma along with the relative lack of other readily available therapeutic options for severe or life-threatening disease, providing patients access to compatible COVID-19 plasma as part of this expanded access protocol appears to reasonably balance potential risks with possible benefit that may outweigh such risks.

**3 OBJECTIVES AND ENDPOINTS**

| OBJECTIVES | ENDPOINTS | JUSTIFICATION FOR ENDPOINTS |
| --- | --- | --- |
| Primary | | |
| Provide access to COVID-19 convalescent plasma | Availability of convalescent plasma | Expanded access protocol |
| Secondary | | |
| Safety | Serious adverse events | Required as part of expanded access protocol under IND |
| Tertiary/Exploratory | | |
| Health care utilization | 1. Acute care facility length of stay 2. Days spent in intensive care unit 3. Survival to acute care facility discharge | Evaluation of potential for efficacy |

**4 STUDY DESIGN**

4.1 OVERALL DESIGN

This is an open-label expanded access program to make appropriately matched convalescent plasma available for the treatment of patients in acute care facilities infected with SARS-CoV-2 who have severe or life-threatening COVID-19, or who are judged by a healthcare provider to be at high risk of progression to severe or life-threatening disease. COVID-19 convalescent plasma will be obtained from blood suppliers and will meet all regulatory requirements for conventional plasma and FDA’s additional considerations for COVID-19 convalescent plasma ([https://www.fda.gov/vaccines-blood-](https://www.fda.gov/vaccines-blood-biologics/investigational-new-drug-ind-or-device-exemption-ide-process-cber/investigational-covid-19-convalescent-plasma-emergency-inds) [biologics/investigational-new-drug-ind-or-device-exemption-ide-process-cber/investigational-covid-19-](https://www.fda.gov/vaccines-blood-biologics/investigational-new-drug-ind-or-device-exemption-ide-process-cber/investigational-covid-19-convalescent-plasma-emergency-inds) [convalescent-plasma-emergency-inds](https://www.fda.gov/vaccines-blood-biologics/investigational-new-drug-ind-or-device-exemption-ide-process-cber/investigational-covid-19-convalescent-plasma-emergency-inds)). Information collected following plasma administration will include serious adverse events, as well as patient demographics, acute care resource utilization, and characteristics of the convalescent plasma administered. Due to the nature of the COVID-19 outbreak, data on patient demographics, acute care resource utilization, and characteristics of the convalescent plasma administered may be collected retrospectively.

4.2 SCIENTIFIC RATIONALE FOR STUDY DESIGN

Convalescent plasma collected from individuals who have recovered from a prior viral infection for the passive transfer of antibodies has been used at various times over the past century. There has

been some evidence for benefit against hepatitis B, polio, measles, influenza, Ebola and other pathogens.^3^ Results from small case series during the prior MERS and SARS coronavirus outbreaks documented safety and faster viral clearance following convalescent plasma administration, particularly when given early in the disease course.^4,3^ Additionally, there is preliminary clinical evidence that suggests that convalescent plasma might provide benefit to individuals with SARS-CoV-2 infection and manifestations of COVID-19.^1,2^ At this time there are few therapeutic options for the treatment of COVID-19 and no prophylactic vaccine is currently available. Based on the preliminary evidence of possible efficacy, this protocol is making convalescent plasma available to individuals with documented SARS-CoV-2 disease at acute care facilities who have severe or life-threatening COVID-19, or who are judged by a provider to be at high risk of progression to severe or life-threatening disease.

4.3 JUSTIFICATION FOR DOSE

Initial data available from studies using COVID-19 convalescent plasma for the treatment of individuals with severe or life-threatening disease indicate that a single dose of 200 mL showed potential efficacy. The volume of plasma to be transfused should be based upon the patient’s weight and clinical comorbidities (e.g. patients with impaired cardiac function and heart failure may require less volume or more prolonged transfusion times). The volume of plasma to be transfused should be at least one unit (approximately 200 mL) but may be greater if the treating clinician concludes a larger volume is appropriate. Transfusions may occur at any time throughout the hospitalization including multiple doses on non-sequential days. In general, it is expected that most patients will receive two units or less, but this language is not intended to restrict the use of convalescent plasma in larger quantities when the treating physician determines that such volumes and/or re-treatment are clinically justified.

4.4 CONVALESCENT PLASMA COMPATIBILITY

ABO compatible convalescent plasma will be transfused preferentially. If ABO compatible convalescent plasma is not available, investigators may follow their institution’s guidelines for administration of incompatible plasma with respect to ABO mismatch, titer, and volume limits.

4.5 END OF STUDY DEFINITION

Patients will complete the study when they are discharged from the acute care facility in which they received the COVID-19 convalescent plasma or 30 days after most recent convalescent plasma transfusion whichever comes first.

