**1 PROTOCOL SUMMARY**

1.1 SYNOPSIS

| **Title:** | Expanded Access to Convalescent Plasma for the Treatment of Patients with COVID-19 |
| --- | --- |
| **Study Description:** | This expanded access program will provide access to investigational convalescent plasma for patients in acute care facilities infected with SARS-CoV-2 who have severe or life-threatening COVID-19, or who are judged by a healthcare provider to be at high risk of progression to severe or life-threatening disease. Following registration on the protocol and provision of informed consent, patients will be transfused with one (or more) units of convalescent plasma obtained from an individual who has recovered from documented infection with SARS-CoV-2. Safety information collected will include serious adverse events. Other information to be collected retrospectively will include patient demographics, acute care facility resource utilization (total length of stay, days in ICU, days intubated, and survival to discharge from an acute care facility. |
| **Objectives:** | Primary Objective: Provide access to COVID-19 convalescent plasma Secondary Safety  Objectives: |
| **Endpoints:** | Primary Endpoint: Availability of convalescent plasma Secondary Endpoints: Serious adverse events |
| **Study Population:** | Patients with severe or life-threatening manifestations of COVID-19, or documented to be at high risk of developing such manifestations |
| **Phase:** | Expanded Access Program |
| **Description of Sites/Facilities Enrolling Participants:** | Acute care facilities treating patients with COVID-19 |
| **Description of Study Intervention:** | Administration of convalescent plasma obtained from donors with prior documented SARS-CoV-2 infection |
| **Study Duration:** | 12 months |
| **Participant Duration:** | Patients will complete the study when they are discharged from the acute care facility in which the received the COVID-19 convalescent plasma. |

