## Statistical Hypotheses

**Primary Hypothesis:** 7-Day and 30-Day mortality will be affected by plasma transfusion dynamics after adjustment for pre-disposing risk factors. Transfusion dynamics are defined in the context of timeliness of transfusion relative to date of diagnosis, the volume of plasma initially given (i.e., on the first transfusion day), and the quantity of neutralizing antibodies on the first day of transfusion.

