## Primary Analysis Plan

### Preparation of the survival endpoint: The timing of death is recorded only with the precision of a calendar day, so adjustments are needed to develop the survival estimates. For deaths that occur on the same day of transfusion, a death indicator representing 0.5 days will be administratively assigned. Otherwise, the number of days between the date of the first transfusion and death will be calculated for each participant. For patients transfused without a death record recorded as an SAE, or more precisely, on the death case report form, they are assumed to be alive. Within the context of the report and programming, this is denoted as the "immortal" survival assumption. To minimize extrapolation of the survival curves beyond a reasonable time that this assumption could be upheld, survival estimates are limited to 30 days; however, the report does introduce stopping the survival curves early, for example, at Day 7 for 7-Day mortality estimates.

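### Participation ends no later than discharge, so the SAP's 30-day mortality is in-hospital death with survival after discharge assumed

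*Supplement*

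**What the plan says.** **End of participation.** Protocol v10.0 section 4.5 closes a patient's participation at discharge or at "30 days after most recent convalescent plasma transfusion whichever comes first". The synopsis (1.1, Participant Duration) has no 30-day limit: "Patients will complete the study when they are discharged from the acute care facility". Section 7.3 describes the protocol as covering acute care only. No section describes contact after discharge.

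**Primary outcome.** The primary hypothesis of SAP v5.0 is that "7-Day and 30-Day mortality will be affected by plasma transfusion dynamics". Under its preparation of the survival endpoint, time runs from first transfusion: "the number of days between the date of the first transfusion and death will be calculated for each participant". For transfused patients with no death recorded as an SAE or, more precisely, "on the death case report form, they are assumed to be alive". The SAP calls this the immortal assumption and, because of it, stops the curves at 30 days.

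**Exploratory outcomes.** Protocol section 3 lists length of stay, ICU days and "Survival to acute care facility discharge", with no time limit. The synopsis plans to collect length of stay and survival to discharge retrospectively, and section 4.1 allows the same for resource utilisation.

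**The concern.** A patient discharged on Day 6 has completed the study. If that patient dies on Day 12, nothing in the protocol causes the death to be found, and the SAP then carries the patient as a survivor to Day 30. The 7-day figure has the same gap for anyone discharged before Day 7.

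The primary comparisons (timeliness, volume and antibody level) are non-randomised. If the groups differ in how soon patients leave hospital, they also differ in how much of the 30-day window is assumed, so the error need not cancel.

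A second, smaller gap lies at the other end. Under section 4.5, a patient still in hospital at the 30-day limit has completed the study before discharge status and total stay are known.

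**Working it through.** The plan states no figure to reproduce. The check compares the follow-up rule with each outcome's window, then illustrates the size.

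**Step 1: what section 4.5 lets one observe, by type of patient**

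| Patient | 30-day mortality from first transfusion | Survival to discharge, length of stay |
| --- | --- | --- |
| (a) Dies in hospital before the limit | Observed | Observed |
| (b) Discharged alive before Day 30 | Observed to discharge, then set to alive | Observed |
| (c) Still inpatient 30 days after last transfusion | Observed | Not observed unless collected later |

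In row (c) mortality is complete because the protocol's clock starts at the most recent transfusion and the SAP's at the first. An inpatient is thus followed for at least 30 days from the SAP's origin. Row (b) is the same under the synopsis; row (c) arises only under section 4.5.

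**Step 2: size of the gap in row (b).** Let *d* be the share discharged alive before Day 30 and *q* their risk of dying between discharge and Day 30. If no such death is captured, understatement = *d* × *q*. The documents give neither, so both are assumptions: *d* = 50-75%, *q* = 1-5%.

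- Low end: 0.50 × 0.01 = 0.005, or 0.5 points.
- High end: 0.75 × 0.05 = 0.0375, or about 3.8 points.

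**Step 3: effect on a comparison.** Assume true 30-day mortality of 25% in both groups, with *d* = 70% in one and 50% in the other, and the same *q*. Apparent relative risk = (0.25 − 0.70*q*) / (0.25 − 0.50*q*).

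- *q* = 1%: 0.243 / 0.245 = 0.992
- *q* = 3%: 0.229 / 0.235 = 0.974
- *q* = 5%: 0.215 / 0.225 = 0.956

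A true value of 1.00 thus appears as about 0.96 to 0.99. Equal *q* matters here. The distortion vanishes when 0.70 × *q*₁ = 0.50 × *q*₂, that is when *q*₁/*q*₂ = 0.50/0.70 = 0.71. If the group discharged sooner has a post-discharge risk below about 71% of the other's, the direction reverses.

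**Step 4: size of the gap in row (c).** Let *m* be in-hospital death before the limit and *s* the share still inpatient at it. Survival to discharge lies between 1 − *m* − *s* and 1 − *m*. With *m* = 25% (assumed):

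- *s* = 2%: 73% to 75%
- *s* = 15%: 60% to 75%

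**The case against.** **Day-30 data may exist.** SAP v2.0, written around 28 May 2020, speaks of outcome data through Day 30 and of a Day-7 follow-up. The protocol's 30-day limit came only with version 8.0 on 16 June. So scheduled outcome forms seem to have coexisted with a discharge-only end of study, and they may have captured some later deaths. This stands as a caution. A reader might infer that the reported figures certainly contain in-hospital deaths only; the forms are not shown, so that is not established. Equally, v2.0 is superseded, and its remark does not show that deaths after discharge were sought. SAP v5.0 does not make being alive depend on a completed Day-30 form.

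**The assumption is disclosed.** The SAP names it and limits the curves because of it. That is fair reporting, but for a discharged patient the extrapolation begins at discharge, and a 30-day limit does not remove it.

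**The discharge outcomes are mostly intact.** A reader might infer that survival to discharge and length of stay cannot be observed at all. The documents do not support that. Only row (c) is affected, only under section 4.5, and the planned retrospective collection may fill it.

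**Death shortens length of stay.** True, but these are exploratory items that SAP v5.0 does not analyse. Replacing them with hospital-free or ICU-free days would be a preference, and would need the same missing post-discharge data.

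**Conclusion.** The point holds for mortality. Under either statement of when participation ends, the plan as written yields in-hospital death through Day 7 or Day 30 and labels it 7-day or 30-day mortality. The absolute understatement is about 0.5 to 3.8 points if 50-75% leave alive early and 1-5% of them die by Day 30. The distortion of a relative risk is modest, about 0.96 to 0.99 for a true 1.00, on the further assumptions of 25% mortality and 70% against 50% early discharge. None of these rates comes from the documents.

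A reader might infer a bias in favour of early transfusion. That requires earlier-transfused patients to be discharged sooner without a correspondingly lower post-discharge risk, and the documents give evidence on neither. Only the possibility of unequal error is supported.

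For discharge status and length of stay the point is narrow: patients still inpatient at the section 4.5 limit, unless their data are completed retrospectively. The two statements of when participation ends do differ and must be reconciled.

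**What to change.** In the SAP, choose one of two routes.

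1. Rename the endpoint *in-hospital mortality through Day 7 / Day 30 after first transfusion* and treat live discharge as a competing event. Where each patient's in-hospital record is complete to Day 30, keeping discharged patients in the denominator already gives the crude cumulative incidence of in-hospital death, so the crude figures need not change. For the adjusted models, state whether discharged patients stay in the risk set (subdistribution hazard) or leave it (cause-specific hazard).
2. Where Day-30 vital status was obtained regardless of discharge, keep the name, censor patients without it at their last known status, and report the alive assumption as a sensitivity analysis. This suits near-complete Day-30 data only, because censoring at discharge treats those sent home as having the same risk as those still in hospital.

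In the protocol, reconcile 1.1 with 4.5. Report survival to discharge and length of stay either to actual discharge or as explicitly truncated at the section 4.5 limit.

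**Cost.** Route 1 needs mainly wording and a model statement, and the mortality claim becomes narrower. Route 2 depends on whether the data exist; obtaining them now would cost the sites effort.

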**5 STUDY POPULATION**

5.1 INCLUSION CRITERIA

1. Age at least 18 years
2. Laboratory confirmed or clinically suspected diagnosis of infection with SARS-CoV-2

Note: Patients enrolled based on clinically suspected infection with SARS-CoV-2 should have pending laboratory confirmation.

1. Admitted to an acute care facility for the treatment of COVID-19 complications
2. Severe or life threatening COVID-19, or judged by the treating provider to be at high risk of progression to severe or life-threatening disease
3. Informed consent provided by the patient or healthcare proxy

Severe COVID-19 is defined by one or more of the following:

- dyspnea
- respiratory frequency ≥ 30/min
- blood oxygen saturation ≤ 93%
- partial pressure of arterial oxygen to fraction of inspired oxygen ratio < 300
- lung infiltrates > 50% within 24 to 48 hours

Life-threatening COVID-19 is defined as one or more of the following:

- respiratory failure
- septic shock
- multiple organ dysfunction or failure

5.2 STRATEGIES FOR RECRUITMENT AND RETENTION

Patients eligible for this Expanded Access Program will be identified by their treating providers and

registered with American Red Cross or other blood source by uscovidplasma.org. Since this involves the administration of COVID-19 convalescent plasma to patients in acute care facilities, participant retention is not anticipated to be an issue.

**6 STUDY INTERVENTION**

6.1 STUDY INTERVENTION(S) ADMINISTRATION

This expanded program will make available compatible COVID-19 convalescent plasma collected by

blood establishments in accordance with the AABB Circular of Information and FDA's regulations and the additional considerations for convalescent plasma on FDA’s webpage ([https://www.fda.gov/vaccines-](https://www.fda.gov/vaccines-blood-biologics/investigational-new-drug-ind-or-device-exemption-ide-process-cber/investigational-covid-19-convalescent-plasma-emergency-inds) [blood-biologics/investigational-new-drug-ind-or-device-exemption-ide-process-cber/investigational-](https://www.fda.gov/vaccines-blood-biologics/investigational-new-drug-ind-or-device-exemption-ide-process-cber/investigational-covid-19-convalescent-plasma-emergency-inds) [covid-19-convalescent-plasma-emergency-inds](https://www.fda.gov/vaccines-blood-biologics/investigational-new-drug-ind-or-device-exemption-ide-process-cber/investigational-covid-19-convalescent-plasma-emergency-inds)).^5^

6.1.1 STUDY INTERVENTION DESCRIPTION

Compatible COVID-19 convalescent plasma will be administered according to standard hospital

procedures.

6.1.2 DOSING AND ADMINISTRATION

For practical purposes in the current outbreak, one – two units of COVID-19 convalescent plasma will be

administered. This will be provided by a registered or licensed blood collector and will be collected preferably by apheresis (total volume of plasma to be administered will be approximately 200 mL or more), or if necessary, by conventional methods (volume of plasma to administer approximately 200- 250 mL per unit). Individual institutional guidelines for the administration of plasma should be followed, including the use of any premedications, such as acetaminophen and diphenhydramine.

**If a subsequent unit of convalescent plasma is transfused**, the treating physician will begin the transfusion at a time that is clinically compatible with the patient’s underlying condition.

6.2 PREPARATION/HANDLING/STORAGE/ACCOUNTABILITY

6.2.1 ACQUISITION AND ACCOUNTABILITY

Convalescent plasma units may be obtained from a registered or licensed blood collector following

registration of the patient.

6.2.2 FORMULATION, APPEARANCE, PACKAGING, AND LABELING

COVID-19 convalescent plasma will be supplied as an investigational blood product for the treatment of

COVID-19.

The container label of COVID-19 convalescent plasma units must include the following statement,

“Caution: New Drug--Limited by Federal (or United States) law to investigational use." (21 CFR 312.6(a)).

In addition, the requirements in 21 CFR 606.121 for the container label applies, including the requirement to include a reference to the circular of information.

6.2.3 PRODUCT STORAGE AND STABILITY

Please see the AABB Circular of Information for product storage and stability.

6.2.4 PREPARATION

Please follow local institutional guidelines for conventional plasma administration for COVID-19 plasma

preparation prior to administration, including compatibility checks and thawing.

6.3 CONCOMITANT THERAPY

Premedications may be administered prior to plasma administration according to individual acute care

facility protocols.

**7 STUDY INTERVENTION DISCONTINUATION AND PARTICIPANT DISCONTINUATION/WITHDRAWAL**

7.1 DISCONTINUATION OF STUDY INTERVENTION

This study involves the administration of COVID-19 convalescent plasma. Patients are free to withdraw

consent from participation at any time.

7.2 PARTICIPANT DISCONTINUATION/WITHDRAWAL FROM THE STUDY

Patients are free to withdraw consent from participation in further data collection at any time during

the study.

Study team encouragement of withdrawal from the EAP as a strategy to avoid completion of follow-up data requirements is not allowed.

7.3 LOST TO FOLLOW-UP

Since this protocol involves only the acute care of individuals with COVID-19, it is not anticipated that

individuals will be lost to follow-up.

**8 STUDY ASSESSMENTS AND PROCEDURES**

8.1 EFFICACY ASSESSMENTS

Patient demographic information will be obtained to include age and sex

Assessments for potential efficacy are exploratory as part of this expanded access program but may include web-based collection of the following information:

1. Acute care facility length of stay
2. Number of days in an intensive care unit
3. Number of days on mechanical ventilation
4. Survival until discharge from an acute care facility

An exploratory analysis may be conducted correlating the level of neutralizing antibody titers with clinical outcomes observed.

8.2 SAFETY AND OTHER ASSESSMENTS

Reporting is required for serious adverse events (SAEs); and we will ask the treating physician when reporting the event to determine if the event is potentially related to the administration of the COVID- 19 convalescent plasma.

